## Methods and analysis

### Study design and sample size calculations

This is a prospective genomic surveillance study of *P. falciparum* samples to be collected between 2024 and 2026 from a variety of transmission intensities and geographies in Mozambique. Sampling design and efforts will be driven by target use cases. A multicluster probabilistic health facility sampling (HFS) sampling scheme^31^ will be followed to detect *pfhrp2/3* deletions and markers of antimalarial resistance across the 10 country provinces (figure 2A). Dried blood spots will be collected from a consecutive sampling of 60 RDT-confirmed malaria clinical cases per health facility, from a systematic random sample of four health facilities per province (figure 2B and table 1). Using the DRpower tool and associated web-based *pfhrp2/3* Planner,^32^ the study power was estimated to detect the prevalence of *hrp2/3* deletions above the 5% threshold at the regional level.^33^ Assuming an intracluster correlation coefficient (ICC) of 0.05 based on historical data (https://mrc-ide.github.io/DRpower/articles/historical_analysis.html), power was estimated at 92.4% (91.9%–92.9%) in regions with three provinces (12 clusters of 60 samples) and 96.9% (96.5–97.2%) in regions with four provinces (16 clusters of 60 samples). Power remains high under the more pessimistic assumption of ICC=0.1, being 78.6% (77.8%–79.4%) and 86.3% (85.6%–87%) for regions with 3 and 4 provinces, respectively. This same design will be used to estimate the prevalence of *pfdhps* mutations at codon 540 at the province level (margin of error analysis). Assuming a mutation prevalence of 90%,^34^ prevalence will be estimated to within 4.8% margin of error for ICC=0.01 and within 7.5% margin of error for ICC 0.05^31^ (assuming lower ICC than for *pfhrp2/3* given the lower variance between clusters expected when looking at smaller geographic scale). Finally, the design will be used to detect the presence of variants of concern (VOCs), namely *pfkelch13* markers of artemisinin partial resistance and *pfdhps-*581 marker of SP resistance, at the province level (presence/absence analysis). Assuming VOCs at 1% prevalence in the population, the design has 85% power to detect VOCs if ICC=0.01 and 67% if ICC=0.05^31^.

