### Enrolment of participants

HFSs will be conducted during the first trimester of 2025. Children aged 2–10 years with fever or history of fever (table 3) will be screened using routine HRP2-based RDTs (First Response Malaria Antigen *P. falciparum* HRP2 [Premier Medical] or SD Bioline Malaria Ag Pf, 05FK50 [Abbott,] depending on national procurement at the time of the study) and an additional confirmatory RDT targeting *P. falciparum* LDH (Biocredit Malaria AG Pf (pLDH) C14RHG25, Rapigen) selected from the recommended options in the WHO master protocol.^33^ Assuming that 85% of samples will be of high sequencing quality, the sample size per health facility will be increased from 60 to 71. Dried blood spots will be collected from study participants if either test is positive, and samples with discrepant RDT results will be used to detect *pfhrp2/3* deletions. The number of people to be screened at each health facility and the duration of recruitment to achieve the sample size will depend on the RDT positivity rate among study participants meeting the eligibility criteria.

**Table 3 T3:** Study eligibility criteria

Inclusion criteria	Exclusion criteria
Children aged 2–10 years of age (cluster sampling). >6 months of age (dense sampling).	Any symptoms of severe malaria.
Fever (axillary temperature≥37.5°C) or history of fever in the preceding 24 hours.	
At least one positive parasitological test for malaria diagnosis via RDT*.	Negative parasitological test for malaria via RDT (except any women at their first ANC visit, who will be recruited before testing for malaria with an RDT).
OR	
Pregnant women (≥12 years of age) attending first antenatal care visit.	Unwilling to provide informed, written consent.
AND	
Informed, written consent to participate from participant and/or guardian.	History of antimalarial treatment in the last 14 days

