### Study outcomes and analysis plan

This project has six primary endpoints. First, prevalence of drug-resistance markers at individual codons, or multicodon haplotypes if successfully phased, will be calculated at provincial level as the number of samples carrying a mutant allele or haplotype out of all samples with a valid genotype for the respective locus. Differences in the prevalence of drug resistance markers (1) between provinces; (2) between years and (3) after interventions will be evaluated using Fisher’s exact test. If emerging VOCs are identified, genetic relatedness between infections will be assessed to describe potential sources and origins of the variants. Allele frequencies will be estimated using methods that account for sample polyclonality.^45^

Second, the prevalence of suspected false-negative HRP2-RDT results among symptomatic patients with *P. falciparum* malaria will be determined at the regional level using the DRpower tool, which accounts for intracluster correlation when estimating the prevalence.^32^ The prevalence of false-negative HRP2-RDT caused by *pfhrp2/3* deletions will be determined as the number of *pfhrp2* or *pfhrp3* deletions confirmed by qPCR^40^ divided by the total number of confirmed cases in a given region.

Third, sources of importation and transmission will be identified using genetic relatedness (identity-by-descent [IBD]) between pairs of samples estimated using Dcifer software.^46^ The fraction of highly related pairs (using a threshold in IBD) will be calculated for samples within each province and between different provinces to characterise the spatial connectivity of parasite genetic populations. Isolation-by-distance will be calculated to assess the extent to which genetic relatedness decreases with geographic distance. Cases from areas targeted for elimination will be classified as local or imported infections by combining data on participants’ reported travel (dates and duration of travel), epidemiologic data from source and destination areas (malaria incidence estimated from DHIS2 data) and genetic data from source and destination areas (relatedness of samples via IBD). Outbreaks will be detected in the study areas using EpiFRIenDs software,^20^ and genetic relatedness analysis within outbreaks will be performed to quantify the number of transmission events causing the outbreak.

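### The within-province fraction of highly related pairs mixes in about 25% same-facility pairs, which the between-province fraction cannot contain, so the contrast depends partly on the sampling layout

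*Protocol article*

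**What the plan says.** The section on study outcomes and analysis plan describes the third of six primary endpoints, the identification of importation and transmission sources through pairwise relatedness. The statistic is introduced as "The fraction of highly related pairs (using a threshold in IBD"; no threshold value is given. It "will be calculated for samples within each province and between different provinces to characterise the spatial connectivity of parasite genetic populations". Two strata are named, and no separate stratum or weight is mentioned for pairs from one facility. The sentence does not say which sampling schemes supply the pairs. The next sentence adds a distance analysis: "Isolation-by-distance will be calculated to assess the extent to which genetic relatedness decreases with geographic distance".

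The section on study design and sample size sets the layout of the facility survey: samples come "from a consecutive sampling of 60 RDT-confirmed malaria clinical cases per health facility, from a systematic random sample of four health facilities per province". Under enrolment of participants, "the sample size per health facility will be increased from 60 to 71" to allow for sequencing failures, and "HFSs will be conducted during the first trimester of 2025" (Table 1 gives January to March 2025).

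Clustering by facility is allowed for elsewhere. The power and margin-of-error figures use an intracluster correlation, and the second endpoint uses DRpower, which accounts for it. No such allowance is stated for the relatedness fraction.

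**The concern.** The two fractions being contrasted do not contain the same kinds of pair. The within-province fraction blends patients from one facility, enrolled one after another in the same quarter, with patients from different facilities in the province. The between-province fraction contains only patients from different facilities. If cases from one facility tend to carry more closely related parasites, the within-province value rises for a reason that works at facility scale, and the amount of the rise is set by how many facilities were drawn. Sampling two or eight facilities instead of four would change the reported value although the parasite population had not changed.

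At stake is the interpretation of the contrast. A difference between the within- and between-province fractions would be described as province-level connectivity when part of it could be relatedness around single facilities.

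**Working it through.** **Inputs from the protocol article**
- Facilities per province in the survey: 4. Cases per facility: 60, consecutive, or 71 collected (study design; enrolment).
- Table 1 lists four survey facilities in each of the ten provinces, with Maputo city and Maputo Province combined as two plus two.
- Not given: the share of highly related pairs of any kind. The values used in steps 3 to 5 are assumptions.

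**Step 1. Confirm the 4 × 60 layout from the plan's own figures**
- Power to detect a variant at 1% prevalence, beta-binomial: 1 − [B(a, b+60)/B(a, b)]^4, with a = 0.01 × (1/ICC − 1) and b = 0.99 × (1/ICC − 1). Result: 84.9% at ICC 0.01 and 66.8% at ICC 0.05 (stated: 85% and 67%).
- Margin of error at 90% prevalence: 1.96 × √[0.9 × 0.1 × (1 + 59 × ICC)/240]. Result: 4.79% and 7.54% (stated: 4.8% and 7.5%).

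All four figures reproduce, so 240 samples in four clusters of 60 is the layout on which the plan relies. No figure is stated for the relatedness endpoint.

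**Step 2. Count the pairs**
- Within a province, all pairs: C(240,2) = 28,680.
- Within a province, same facility: 4 × C(60,2) = 4 × 1,770 = 7,080.
- Share: 7,080/28,680 = 24.7%. With 71 per facility: 9,940/40,186 = 24.7%.
- Between two provinces: 240 × 240 = 57,600 pairs, of which 0 share a facility.

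For scale, the caption of Figure 2 gives between 114 and 224 facilities per province (Maputo Province and city combined: 128). If cases were spread evenly over them (an assumption), same-facility pairs would be about 0.4% to 0.9% of all pairs in the province.

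**Step 3. Effect on the contrast**

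Within-province fraction = s × f_same + (1 − s) × f_other, with s = 0.247. Assume different-facility pairs are equally related within and between provinces, at 0.5%, so that there is no province-level structure to find.

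| Same-facility pairs highly related (assumed) | Within-province fraction | Within/between ratio | Ratio from different-facility pairs only |
|---|---|---|---|
| 0.5% | 0.50% | 1.0 | 1.0 |
| 1% | 0.62% | 1.25 | 1.0 |
| 2% | 0.87% | 1.7 | 1.0 |
| 5% | 1.61% | 3.2 | 1.0 |

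**Step 4. The same with real province structure**

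Assume 2% for same-facility pairs, 1% for different-facility pairs in the province and 0.5% between provinces. The pooled within-province fraction is 0.247 × 2% + 0.753 × 1% = 1.25%, a ratio of 2.5. Different-facility pairs give 2.0. The structure is present but overstated.

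**Step 5. Dependence on the number of facilities**

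Hold 240 samples, with f_same = 2% and f_other = 0.5%.
- Two facilities: share 49.8%, fraction 1.25%.
- Four facilities: share 24.7%, fraction 0.87%.
- Eight facilities: share 12.1%, fraction 0.68%.

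**Step 6. If schemes were mixed**

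The text does not say that they will be. With equal clinic sizes, antenatal samples from three, two or one clinics would have same-facility shares of about 33%, 50% or 100%; Table 1 lists one such clinic in Nampula. The 290 + 630 + 550 = 1,470 dense samples in Maputo Province lie across 34 facilities (Table 2). With an even split within each group they would have a share of about 3%, and about 2.7% when pooled with the 240 survey samples.

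**The case against.** The article condenses a fuller protocol, and the choice of pairs may be settled there. That could be so, but the article does more than leave a gap: it names two strata and a purpose, and followed as written they are not like for like.

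Relatedness among patients of one facility is real, fine-scale spatial structure and not an artefact. This stands. The fault is narrower: that structure enters a province-level quantity with a weight set by the design.

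The planned isolation-by-distance analysis places same-facility pairs at or near zero distance, so an excess there can be seen. This also stands in part. It can reveal the excess, but it leaves the province contrast uncorrected.

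The size is unknown. The intracluster correlations in the article concern marker prevalence and cannot be carried over to IBD. With no same-facility excess, the ratio is 1.0 and nothing is distorted.

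Three stronger readings are tempting, and the document supports none of them:
- A reader might infer that provinces will necessarily look more isolated than they are. That requires a same-facility excess, which is plausible but not given.
- A reader might infer that the identification of national sources and sinks is biased. Between-province fractions contain no same-facility pairs, so comparing which provinces connect to which is untouched by this mechanism. The discussion also plans other models for sources and drivers of transmission, and nothing says that the within/between contrast decides the matter.
- A reader might infer that Maputo is not comparable with the other nine provinces. Every province has four survey facilities and hence about the same 24.7% share. A difference would arise only if dense samples were pooled in, which the article does not state, and pooling would lower Maputo's same-facility share.

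**Conclusion.** The point holds in a limited form. Taken over all survey samples, the within-province fraction includes 24.7% same-facility pairs and the between-province fraction includes none. That follows from the stated layout, assuming equal numbers per facility. Whether this distorts the contrast depends on how much more related same-facility pairs are, which the document does not say. Over the assumed range of 0.5% to 5%, with other pairs at 0.5%, the within/between ratio runs from 1.0 to 3.2. The defensible statement is that the contrast can overstate province-level structure by an amount tied to the number of facilities sampled. It is a worthwhile change to make before analysis, and it does not show that the endpoint fails.

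**What to change.** 1. Report three fractions of highly related pairs: same facility; different facility in the same province; different provinces.
2. Base the within/between province contrast on different-facility pairs.
3. Compute the main national contrast from the facility-survey samples, so that the same-facility share is alike across provinces. Add antenatal or dense samples only as separate or sensitivity analyses, and state which scheme supplies the pairs.
4. Do not treat pairs as independent when giving uncertainty: each of 240 samples enters 239 within-province pairs. Resampling whole facilities is one route, but with four per province the province-level intervals will be unstable and should be described as such.

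No new data are needed, only a pair filter in the relatedness analysis. The cost is that about a quarter of within-province pairs (7,080 of 28,680) move to their own category, leaving 21,600 for the contrast.

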	HC Salamanga	
	HC Hindanne	
	HC Matutuine	
	HC Nsime	
	HC Santa Maria	
Namaacha	HC Changalane	August 2024–August 2025
	HC Kulula	
	HC Matsequenha	
	HC Odete Mechisso	
	HC Dibinduane	
	HC Mundavene	
	HC Wamongo	
	HC Goba	
	HC Mahelane	
	HC Mafuiane	August 2024 until 50 samples collected
	HC Namaacha	

HChealth center

Pregnant women will be tested for *P. falciparum* malaria at their first ANC visit to assess malaria trends and MMS. During the first 2 years (January 2024 to December 2025), 1–3 ANC clinics per province will be selected (figure 2D; table 1) based on the average number of monthly recruitments in each province during 2023. Approximately 1300 samples are expected per each of the 10 provinces per year. Of the 13 000 samples collected across the country per year (total 26 000), 2870 are expected to be positive for *P. falciparum* by RDT (total 5740), based on the RDT-positivity rates obtained in 2023 at each province.

Finally, targeted sampling will be conducted at sentinel health facilities (figure 2E) in the four districts (Cuamba in Niassa, Mopeia in Zambézia, Dondo in Sofala and Massinga in Inhambane) where children aged 6–59 months (n=87 children per site) with microscopically confirmed uncomplicated *P. falciparum* malaria will be recruited for a TES.

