* Routine one (First Response Malaria Antigen HRP2 [Premier Medical Inc] or Bioline Malaria Ag Pf, 05FK50 [Abbott], depending on national procurement at the tiem of the study) plus a second RDT (BIOCREDIT Malaria Ag pLDH), the latter being provided to support detection of deletions.Routine RDT (First Response® Malaria Antigen *P. falciparum* HRP2 [Premier Medical Inc] or SD Bioline Malaria Ag Pf [Abbott, 05FK50], depending on national procurement at the time of the study) plus a second confirmatory RDT (BIOCREDIT Malaria Ag Pf pLDH, Rapigen Inc), the latter being provided to support detection of *P. falciparum* parasites with *pfhrp2* deletions

ANCantenatal careRDTrapid diagnostic test

Women attending their first ANC visit (table 3) will be invited to participate in the study (if they live in the study area) by trained nurses, who will assign a unique identification number to consenting and eligible women and complete a brief form including date of visit, mother’s age, gravidity, week of pregnancy, area of residence and recent or past movements. Women will also be asked about health-seeking behaviours and use of interventions. Finally, women will be finger pricked for malaria RDT along with routine tests, treated if positive and a dried blood spot collected on filter paper for molecular analysis.

Dense sampling in Magude, Matutuine and Namaacha districts will be coordinated with district malaria focal points, community health workers (CHW), malaria volunteers (who provide a link between the CHW and the health facility, and assist the CHW in the follow-up of cases and administration of medication) and health facilities. All *P. falciparum* positive RDTs (SD Bioline Malaria Ag Pf, 05FK50, Abbott) among clinical cases (>6 months old; table 3) will be stored for molecular analysis. Once a case is notified, field workers will travel to the household of the case to collect Global Positioning System location within the period of 3 days (up to 7 days if needed).

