Fourth, genetic diversity metrics will be assessed to characterise natural and intervention-driven changes in transmission.^13^,^1647 48^ Correlation analysis will be used to test the relationship between parasite genetic diversity metrics (locus-based expected heterozygosity), within-host diversity data (multiplicity of infection [MOI] and effective MOI,^45^ Wright’s inbreeding coefficient, the proportion of polyclonal infections), the proportion of highly related samples based on IBD), RDT positivity rates at ANC clinics and DHIS2-based malaria incidence, the latter corrected for several potential biases (health-seeking behaviour, reporting and testing and alternative causes of fever).^1^ The use of microhaplotype-based genetic diversity markers to discriminate recrudescence from new infections in TESs will be compared with the currently recommended WHO/MMV *msp1*/*msp2*/*polyA*.^49^ In addition, the genetic diversity in the C-terminal region of the circumsporozoite protein that encompasses T-cell epitopes included in the R21/Matrix-M^23^ and RTS,S^28^ malaria vaccines will be determined by comparing the sequence reads with those in the *P. falciparum* 3D7 reference genome.

Finally, *P. falciparum* parasite rates and genomic indicators will be generated for the first ANC visit. RDT positivity rates and Insecticide-treated nets/indoor residual spraying coverage data will be compared with unbiased gold standard household-level data collected through the Malaria Indicator Survey. Time series analysis and logistic multivariate regression will be considered to assess seasonality and to estimate the change in parasite rates after introduction of antimalarial interventions, including an interaction term, area#timepoint, to identify effect differences among interventions introduced in the country (chemoprevention, malaria vaccine, vector control). A mechanistic transmission model, malariasimulation (https://mrc-ide.github.io/malariasimulation/), will be fitted to monthly ANC prevalence, adjusted for gravidity, using the siftr R package developed by Imperial College London to generate estimates of transmission and potential clinical case burden. Rates of polymorphisms associated with antimalarial, diagnostic and vaccine resistance will be compared in parasites collected from pregnant women and the general community.

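### The planned comparison of pfhrp2/3 deletions between pregnant women and the community is not like for like: only the facility survey has a described route for HRP2-negative infections

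*Protocol article*

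**What the plan says.** All references are to the protocol article.

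- **Planned comparison** (Study outcomes and analysis plan, antenatal endpoint): "Rates of polymorphisms associated with antimalarial, diagnostic and vaccine resistance will be compared in parasites collected from pregnant women and the general community". The source of the community samples is not named.
- **Facility survey** (Enrolment of participants): febrile children have a routine HRP2 test and a pLDH test. A positive result on either is enough for a blood spot, and "samples with discrepant RDT results will be used to detect *pfhrp2/3* deletions". The footnote to Table 3 says that the second test is there to support finding deletions.
- **Antenatal scheme** (Enrolment of participants): "women will be finger pricked for malaria RDT along with routine tests, treated if positive and a dried blood spot collected on filter paper". The product is not named and no pLDH test is mentioned. Table 3 excludes people with a negative test "except any women at their first ANC visit, who will be recruited before testing for malaria with an RDT".
- **Antenatal yield** (Study design and sample size calculations): of 13 000 samples a year, 2870 "are expected to be positive for *P. falciparum* by RDT (total 5740" over two years), based on 2023 positivity of the rapid test.
- **Dense sampling** (Enrolment of participants): the material stored is "positive RDTs (SD Bioline Malaria Ag Pf, 05FK50, Abbott) among clinical cases", a single product with no pLDH test.
- **Laboratory work** (Molecular analyses): about 7690 samples go to amplicon sequencing, a number derived from expected positivity. The panel includes pfhrp2/3 targets, and qPCR confirms deletions.

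**The concern.** A pfhrp2 deletion matters because it can turn the HRP2 test negative. A sample chosen for genotyping because that test was positive has therefore been selected on the outcome under study. The survey guards against this with its second test. The antenatal scheme, as described, has no equivalent: with one test there can be no discrepant result, and no other HRP2-independent route to a deletion is set out.

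The Discussion presents antenatal samples as a complement to the survey. The evidence it cites for agreement between pregnant women and children concerns diversity, relatedness and drug-resistance markers, not deletions. A lower deletion rate in pregnant women could be read as biology, or as reassurance about HRP2-based testing, when it came from how infections entered the data set. Only the diagnostic marker is affected in this way.

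**Working it through.** **1. The plan's own antenatal figures.** 1300 × 10 provinces = 13 000 a year, and × 2 = 26 000. 2870 × 2 = 5740. 2870/13 000 = 22.1%. These agree with the article. They also show that spots from RDT-negative women are collected, about 13 000 − 2870 = 10 130 a year.

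**2. Does the sequencing total show which antenatal spots are genotyped?** No. The survey gives 40 × 60 = 2400. Dense sampling gives 290 + 630 + 550 = 1470. The efficacy studies give 4 × 87 = 348. The survey and the antenatal positives alone make 2400 + 5740 = 8140, already above 7690. No combination of the stated scheme totals gives 7690 exactly. Genotyping by RDT positivity is therefore the natural reading of a yield expressed that way, but it remains an inference.

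**3. Size of the bias if antenatal genotyping follows a positive HRP2 test.** Let

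- p = true share of infections with a deletion, the same in both groups (assumed);
- w = HRP2-test sensitivity without a deletion, 0.95 (assumed);
- s = chance that a deletion infection still tests HRP2-positive, for example in a mixed infection or with a pfhrp3-only deletion (assumed, 0 to 0.5).

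Observed antenatal share = p·s / (p·s + (1 − p)·w).

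For p = 0.05 and s = 0.25: 0.0125 / (0.0125 + 0.9025) = 1.4%. For p = 0.05 and s = 0.5: 0.025 / (0.025 + 0.9025) = 2.7%.

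| True p (about the survey share) | s = 0 | s = 0.1 | s = 0.25 | s = 0.5 |
|---|---|---|---|---|
| 1% | 0% | 0.11% | 0.27% | 0.53% |
| 5% | 0% | 0.55% | 1.4% | 2.7% |
| 10% | 0% | 1.2% | 2.8% | 5.5% |

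The survey share is close to p if the either-test rule catches infections with and without deletions about equally, and if survey samples positive on both tests are also read for deletions on the panel.

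**4. Chance of declaring a difference that does not exist.** Take a three-province region with 12 × 60 = 720 survey samples and 3 × 287 = 861 antenatal positives in one year (2870/10 = 287 per province). Use a two-sided 5% test and ignore clustering.

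| True p | s = 0 | s = 0.1 | s = 0.25 | s = 0.5 |
|---|---|---|---|---|
| 1% | 82% | 69% | 47% | 20% |
| 5% | 100% | 100% | 98% | 67% |
| 10% | 100% | 100% | 100% | 91% |

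Clustering lowers these chances. At the plan's ICC of 0.05, the survey design effect is 1 + 59 × 0.05 = 3.95, so 720 samples carry the information of about 720/3.95 = 182. The bias in step 3 does not depend on clustering.

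**5. Where the missing infections would be.** With p = 5%, s = 0 and w = 0.95, 2870 positives imply 2870/(0.95 × 0.95) = 3180 infections. Of these, 5%, or 159 a year, carry deletions and lie among the RDT-negative spots. For p = 1% and 10% the figures are about 31 and 336.

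**6. If dense sampling is the comparator.** Both sides then keep only positives of a single test. The built-in difference may disappear, but both under-count, and agreement would say little about deletions.

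**The case against.** The strongest objection is that a reader might infer that pregnant women are selected by a positive HRP2 test. The article does not say so. They are recruited before testing, and in "treated if positive and a dried blood spot collected on filter paper for molecular analysis" the positive result is tied to treatment; the spot is not said to depend on it. The antenatal test is never named; that it is HRP2-based is inferred from the routine tests named elsewhere. No section says that RDT-negative spots will go unscreened, and qPCR for density, species and deletions is listed without any such restriction. All of this stands, and it makes the bias conditional.

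A reader might also infer that the comparison is bound to show deletions missing in pregnancy, with a vanishingly small p-value: 36/720 against 0/861 gives a Fisher p of about 3 × 10⁻¹³. The documents do not support that either. It takes s = 0, treats the 5% decision threshold as an expected prevalence, and ignores clustering.

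It can further be said that the undefined community group and the unstated genotyping rule are details for the full protocol. That is fair for each detail alone. But the article itself commits to the comparison, and it fixes two tests on one side while describing one on the other. Nor is the problem beyond repair from planned data: the survey records both results, so it can be restricted to HRP2-positive children.

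**Conclusion.** The point holds in conditional form. As written, the plan does not give a like-for-like pfhrp2/3 comparison between pregnant women and the community. If antenatal genotyping follows HRP2-test positivity, deletions are under-counted there relative to the survey: about 0 to 2.7% against 5%, under the assumptions p = 5%, w = 0.95 and s between 0 and 0.5. If all antenatal spots were screened independently of HRP2, the expected antenatal share would equal p and this artefact would vanish. The article does not describe that step.

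The issue is confined to the diagnostic marker in one comparison. The regional deletion endpoint, which rests on the two-test survey and DRpower, is not affected, and nothing in the article proposes using antenatal or dense samples to declare deletions absent. The change should be made because it is cheap and prevents a misreading.

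**What to change.** - Keep the comparison between pregnant women and the community for drug-resistance and csp markers, and name the community source.
- For pfhrp2/3, either remove it from this comparison, or restrict both groups to HRP2-RDT-positive samples and label the result as deletions among HRP2-positive infections. The second option requires stating which test is used at antenatal clinics. It also requires reading deletions from the panel and confirmatory qPCR in both groups, since discrepant results play no part there. It is fair only if w and s are similar in the two groups.
- State that deletion prevalence is estimated only from the two-test survey, and that antenatal and dense samples selected by an HRP2 test are not used to estimate it or to rule deletions out.
- Optional: parasite qPCR, then pfhrp2/3 qPCR, on a random subset of the RDT-negative antenatal spots, weighted back by the sampling fraction. Under step 5 with p = 5%, deletion infections make up 159/10 130 = 1.6% of those spots, so 1000 spots would hold about 16. With p = 1% it would be about 3.

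The first three changes cost a few sentences and no data. The last costs laboratory work on spots that are already collected, with assays already planned.
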